## Abstract

**Introduction:**

Physical activity is important for healthy ageing. Despite strong evidence on the benefits of physical activity for health and well-being, physical inactivity remains a significant problem among older adults. This study aims to determine the feasibility and acceptability of implementing an online volunteer-led group exercise for older adults.

**Methods:**

A quasi-experimental mixed-methods approach will be used in this study. A training programme will be developed to train volunteers to deliver online group exercises to older adults aged >65 years (n=30). The primary outcome is the feasibility of implementing the intervention. This will be assessed by the number of volunteers recruited, trained, and retained at the end of the study, and the number of exercise sessions delivered and completed by participants. Secondary outcomes include physical activity levels measured using the Community Health Model Activities Programme for Seniors questionnaire, Barthel Index, EQ-5D-5L as a measure of health-related quality of life, SARC-F to determine sarcopenia status, and PRIMSA-7 to determine frailty status. Outcomes will be measured at baseline and at 6 months.

Qualitative interviews will be conducted with volunteers(n=5), older adults (n=10) and family members (n=5) to explore their views on the intervention.

**Analysis:**

Simple descriptive statistics will be used to describe participant characteristics, the feasibility of the study and the impact of the intervention on health outcomes. Parametric(t-test) or non-parametric(Mann-Whitney U test) statistics will be used to analyse continuous variables. χ^2^ test will be used for categorical variables. Qualitative data will be analysed using an inductive thematic analysis approach.

**Ethics and dissemination:**

This study received ethical approval from the University of Southampton Faculty of Medicine Ethics Committee and Research Integrity and Governance committee (ID: 52 967 .A1). Study findings will be made available to service users, voluntary organisations and other researchers who may be interested in implementing the intervention.

**Trial registration number:**

NCT04672200.

Strengths and limitations of this studyThis is a novel study exploring the use of trained volunteers to deliver online group exercises for older adults.It addresses the issue of physical inactivity among older people, a problem which has been exacerbated by the COVID-19 pandemic.A mixed-methods approach will support the development of a toolkit for future implementation.For safety reasons, volunteers will deliver seated exercises in online groups.The exclusion of older adults who are not able to provide consent limits the generalisability of this study.

## Introduction

Physical activity is important for healthy ageing. Some of the benefits of regular physical activity for older people include reduction in falls,^1^ better physical functioning^2^ and improvement in well-being.^3^ The recommended physical activity level for older adults aged 65 years and above is to achieve 150 min of moderate physical activity in a week, with 2 days of strength training.^4^ This is often expressed as 30 min of brisk walking or equivalent activity 5 days a week, although 75 min of vigorous intensity activity spread across the week, or a combination of moderate and vigorous activity are also suggested.^5^

Despite strong evidence for the benefits of physical activity, physical inactivity remains a significant problem among older adults worldwide.^6^ Studies in the UK have shown that less than 7% of community-dwelling older adults achieve the recommended weekly physical activity level.^7 8^ The COVID-19 pandemic has exacerbated the problem of physical inactivity.^9^ Rules on social distancing and shielding of vulnerable groups have resulted in increased physical inactivity among older people, with potentially widespread deconditioning.

The rise of the use of technology during the pandemic may provide a solution to address the problem of physical inactivity among older people. Older adults are embracing modern technology more than ever before and are increasingly familiar with the use of devices and online platforms to stay in touch with their family members and friends.^10 11^ This presents the opportunity to develop online physical activity interventions for older adults to promote increased physical activity. A review of reviews conducted by McGarrigle and Todd found low to moderate evidence that physical activity interventions delivered through the internet and related technologies may be effective in increasing physical activity among older adults in the short term.^12^ Online group exercises have been shown to be feasible for older adults.^13^ However, there is little evidence on the use of trained volunteers to lead such exercise groups.

Volunteers play an integral part within many health and social care organisations. They enrich patient experience, help deliver high quality services, and support communities in living healthier lives.^14^ A report by the King’s Fund on volunteering has highlighted that the support volunteers provide can be of particular value to those who rely most heavily on services, such as people with multiple long-term conditions or mental health problems.^15^ There is increasing evidence to suggest that with proper training, volunteers can take on more direct roles in supporting older adults particularly with nutrition^16^ and mobility.^17^

The Southampton Mobility Volunteer study (n=100, mean age 86 years) showed that volunteers can be trained to deliver chair-based exercises to older adults admitted to hospital.^17^ The intervention was shown to be safe, and acceptable to older adults and healthcare professionals, with evidence of improvement in daily step count among patients who received the intervention. The median age of the volunteers in the study was 32 years (interquartile ratio of 17–62 years). A systematic review of 12 studies found some evidence suggesting that volunteer-led physical activity interventions that include resistance exercise training, can improve outcomes of community-dwelling older adults including functional status, frailty status and reduction in fear of falls.^18^ However, knowledge gaps still exist on how best to recruit, train, and retain volunteers to deliver physical activity interventions routinely. This study addresses this knowledge gap by exploring facilitators and barriers to the implementation of volunteer-led group exercises for older adults attending social clubs.

Older adults who volunteer to lead physical activity interventions also benefit from their volunteering, with one study showing evidence of improved physical activity levels.^19^ Older volunteers also benefit from the social interaction that volunteering brings, with reduced feelings of loneliness and having a sense of achievement.^20^ The use of trained volunteers to deliver online physical activity interventions remains an under-researched area and this study addresses the important knowledge gap on the feasibility and acceptability of such interventions.^21^

### Aims

This study aims to determine the feasibility and acceptability of training volunteers to deliver online group exercises to community-dwelling older adults. The specific objectives of this study are to:

Develop a training programme for volunteers to lead online group exercises.Determine the feasibility of recruiting, training and retaining volunteers to deliver the online intervention.Determine the acceptability of the online intervention to volunteers, older adults and their carers.Explore barriers and facilitators to the implementation of the online intervention.

## Methods and analysis

### Study design

A quasi-experimental mixed-methods approach will be used to determine the feasibility and acceptability of implementing online volunteer-led exercise sessions in community clubs. The study will be conducted at community-clubs focused on promoting social interaction among older people. Feasibility studies are used to determine whether an intervention is appropriate for further evaluation, to determine sample sizes for controlled trials and to assess whether the ideas and findings can be shaped to be relevant and sustainable. In this study, the feasibility of training volunteers to promote increased physical activity among community-dwelling older adults will be assessed. The acceptability of the intervention will be examined through qualitative interviews to explore the views and experiences of volunteers, older adults participating in the study, and their carers or family members. The impact of the intervention on physical activity levels and functional outcomes will also be measured. This will help inform the sample size calculation for a future effectiveness trial.

### Participant recruitment

#### Volunteer recruitment

The research team will be invited by club staff to attend the virtual clubs to introduce the study. Club volunteers and members who are interested in leading the group exercise will indicate their interest to staff members or approach the research team directly. To lead the group exercise, volunteers must be physically able to perform the exercises themselves and be able to provide written consent. This will be assessed at the training sessions by the trainer (SM).

The participant information sheet and the consent form will be sent through the post. Club members are invited to contact the research team for further discussions about the study. Once the research team has received the signed consent form, volunteers will be invited to participate in the online training. To deliver online group exercise to 30 exercise participants, it is estimated that at least 12 volunteers will be needed to lead 6 online groups. Volunteers will be paired up to lead and deliver the intervention.

#### Volunteer training

The volunteer training programme will be led by a member of the research team with a background in sport and exercise science. The training programme was developed based on clinical expertise from therapists and current evidence including experience from a recently completed hospital-based study.^17^

The training will be delivered online through Zoom. Each volunteer will receive two group training sessions, lasting an hour each, and further one to one sessions will be offered to volunteers who wish to have further training. At the first training session, volunteers are given an overview on the importance of physical activity. They are introduced to their role in greater detail and given the opportunity to ask questions. They will be taught the exercise protocol, including the warm up and cool down exercises. The trainer will demonstrate the exercises and provide guidance on how to perform the exercises accurately. They will also be taught the purpose and benefits of each exercise performed. Volunteers will receive training on how to lead the group well, with practical guidance such as being confident, speaking with a clear voice, pacing themselves and providing positive encouragement to the participants. This is then followed by a practical session where the volunteers will practice leading the exercise among the training group members. The training session will also include key aspects such as personal safety and safety of participants. Examples of personal safety include ensuring appropriate clothing and footwear, having good ventilation in the room, staying well-hydrated, and adopting a correct posture while performing the exercises. Volunteers will be trained to coach the participants, ensuring that the exercises are performed safely and effectively to prevent injuries. They will receive training on how to document adverse events that occur during the exercise classes. They will also be given guidance on how to set up their digital devices. Volunteers will receive a training booklet containing the exercises and safety instructions, as well as an exercise video to support their training. Competency assessments based on a checklist will be conducted by the research team to ensure that volunteers are competent in delivering the exercises (online supplemental file 1).

10.1136/bmjopen-2021-052631.supp1Supplementary data

The emphasis of the second training session will be to provide opportunity for the volunteers to practice leading the group sessions. The trainer will observe the volunteers as they lead the exercises and provide feedback to ensure that they are performed accurately. They will also be given advise on how to set up the exercise space to ensure there is adequate space for the exercises to be performed safely, and that the device is optimally set up for participants to see them performing the exercises clearly.

Throughout the study period, fidelity checks will be conducted to ensure that the volunteers are delivering high quality exercise sessions. The fidelity checks will comprise assessment of the volunteer exercise delivery including the safe and effective demonstration and instruction of the warm-up, strength exercise and cool down components of the exercises. A member of the research team will attend the group online sessions as an observer to conduct the checks. Volunteers who require further support in delivering the exercises will be offered additional coaching by the research team to ensure that the exercises are delivered correctly.

Regular meetings for the volunteers will be held throughout the study period to provide them with ongoing support from the research team and the organisation running the online clubs. The group meetings will provide an avenue for volunteers to discuss and share their experiences, ask questions and provide suggestions to improve the intervention.

#### Exercise participant recruitment

Club members who are interested in participating in the online group exercise will indicate their interest to club staff or approach the research team directly. Participant information sheet and consent forms will be posted to club members.

The inclusion criteria for the group exercise participants are: adults aged 65 years and older, able to walk with or without a walking aid, and able to provide written consent (box 1). Participants who are actively participating in other online exercise classes will be excluded. The aim is to recruit 30 older adults attending social clubs who do not engage in regular exercise.

Box 1Inclusion and exclusion criteriaInclusion criteriaOlder adults aged >65 years.Able to walk, with or without a walking aid.Able to provide written consent.Exclusion criteriaActively participating in other online exercise classes.

### Intervention

The intervention consists of a once weekly volunteer-led online group home-based exercise, for a duration of 30 min. The online group will be led by volunteers and hosted on the digital platform Zoom.^22^ To comply with the social club’s online insurance policy and to minimise the risk of injury to participants, the intervention will only include seated exercises. The seated exercises will focus on strengthening upper and lower limbs and enhancing whole body range of motion and flexibility, tailored specifically to meet the needs of older adults through considering appropriate frequency, intensity, time, type principles and exercise adaptations (eg, in response to joint pain and discomfort). Participants will be encouraged by the volunteers to progress by increasing repetitions and to gently improve range of motion. No supplementary equipment is needed for the online exercises. In addition to the group exercise sessions, participants will also be encouraged to increase mobility and physical activity levels through use of a home activity booklet, including a physical activity diary. The exercise sessions will be piloted in one club before being extended to other clubs.

### Outcomes measures

Volunteer characteristics such as age, gender, employment status, previous volunteering experience and experience in delivering group exercises will be recorded. Participant characteristics including age, gender, domicile status, body mass index, co-morbidities, cognition (telephone Mini-Mental State Examination) and number of medications will be recorded.

#### Primary outcomes

The primary outcome of this study is the feasibility of implementing volunteer-led online group exercise for older adults. This will be assessed by determining:

The number of volunteers recruited, trained and retained at the end of the study.The number of physical activity sessions delivered and completed by participants (adherence).The fidelity of the exercise intervention delivered by volunteers.

#### Secondary outcomes

The secondary outcome measures include measurement of physical activity levels and performance of activities of daily living (ADLs). Physical activity levels will be measured using the Community Health Model Activities Programme for Seniors (CHAMPS) questionnaire.^23^ The questionnaire assesses self-reported weekly frequency and duration of various physical activities typically undertaken by older adults, and is a validated measure of physical activity for older people.^24^ Performance of ADL will be measured using the Barthel Index.^25^ The Barthel Index measures ADL including transfers, walking, stairs, toilet use, dressing, feeding, bladder control, bowel control, grooming and bathing, to give a maximum total score of 100. It is a validated measure of ADL that is recommended for use in research among older people.^26^ TheEuroQol - 5 Dimension (EQ-5D-5L) measure developed by the EuroQol group will be used to determine health-related quality of life.^27^ The measure comprises five dimensions: mobility, self-care, usual activities, pain/discomfort, and anxiety/ depression. Each dimension is given a 1-digit score and the digits for the five dimensions are combined unto a 5-digit number that describes the patient’s health state. The measure is commonly used in research among older people.^28 29^ The Strength, Assistance with walking, Rising from a chair, Climbing stairs, and Falls (SARC-F) questionnaire will be used as a measure to assess for sarcopenia.^30^ According to recent guidelines from the European Working Group on Sarcopenia in Older People, SARC-F is the recommended tool for sarcopenia case finding.^31^ It comprises five components: strength, assistance in walking, rise from a chair, climbing stairs and falls. The scores range from 0 to 10, with a score of equal to or greater than four being predictive of sarcopenia and poor outcome. Program of Research to Integrate Services for the Maintenance of Autonomy (PRISMA-7) screening tool will be used to characterise participants’ frailty status.^32^ The questionnaire contains seven items with a positive score of three or more indicating frailty. The PRISMA-7 tool has been shown to have high accuracy in identifying frail older adults in the community setting.^33^

These outcome measures will be recorded at baseline, using remote assessment formats (eg, telephone based) and repeated at 6 months. Cost analysis will be conducted to determine the cost of implementing this intervention. The analysis will include the cost of training the volunteers, taking into consideration the time needed to deliver the group training sessions and the individual competency assessments, and the provision of training materials.

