### Data analysis plan

#### Quantitative data analysis

Data collected will be double entered into a secured database for analysis. Statistical analysis will be conducted using the statistical software SPSS Statistics V.25. Descriptive statistics—median (IQR); mean (SD); number (%)—will be used to analyse the numbers of volunteers recruited, trained, and retained, as well as the type and extent of progression of the seated exercise, and duration of their activity, and patients’ adherence to the intervention. Analysis of the above outcome measures will be used to develop an assessment of the feasibility of delivering this intervention. Adherence to the intervention and reasons for non-adherence will be reported.

Outcome measures recorded at baseline will be compared with measurement at 6 months to determine if the PA intervention had an impact on physical activity levels measured by CHAMPS, functional outcomes including performance in ADLs (Barthel Index), quality of life (EQ-5D-5L), frailty status (PRISMA-7) and sarcopenia status (SARC-F). The distribution of each outcome measure will be assessed for normality. Depending on the skew of the data, parametric (t-test) or non-parametric (Mann-Whitney U test) statistics will be used for continuous variables. χ^2^ test will be used for categorical variables.

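### SARC-F and PRISMA-7 are named for comparison as sarcopenia and frailty status, which hides score change that does not cross the cut-off; the EQ-5D-5L quantity to be compared also needs stating

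*Protocol article*

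**What the plan says.** The Secondary outcomes section of the protocol article gives a scoring description for each of the three instruments.

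- **SARC-F:** "The scores range from 0 to 10, with a score of equal to or greater than four being predictive of sarcopenia and poor outcome".
- **PRISMA-7:** "The questionnaire contains seven items with a positive score of three or more indicating frailty". Its stated use is that the "screening tool will be used to characterise participants’ frailty status".
- **EQ-5D-5L:** it "will be used to determine health-related quality of life", and "Each dimension is given a 1-digit score and the digits for the five dimensions are combined unto a 5-digit number". The article presents this number as a description of the health state. It mentions no index value, visual analogue score or analysis by dimension.

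The Quantitative data analysis section lists the outcomes to be compared between baseline and 6 months, among them "quality of life (EQ-5D-5L), frailty status (PRISMA-7) and sarcopenia status (SARC-F". The Methods paragraph of the abstract also ties SARC-F to sarcopenia status and PRISMA-7 to frailty status. On tests, "parametric (t-test) or non-parametric (Mann-Whitney U test) statistics will be used for continuous variables", and χ² is assigned to categorical variables. The distribution of every outcome measure is to be checked for normality.

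The Study design section says that the measured impact on activity and function will help to set the sample size of a later effectiveness trial. The recruitment target is 30 exercise participants.

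**The concern.** Two ordered scores are collected, but the analysis section names them by their dichotomised form. A before-after comparison of status registers only people who cross the cut-off. Someone well above or well below it can change by several points without any effect on the result, while a one-point move across the line counts in full.

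Two things are at stake. With at most 30 people, a status comparison could look flat when the scores have moved. And planning a later trial on either scale needs the SD of score change, which a table of status does not supply.

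For EQ-5D-5L the risk is one of misreading. The profile is called a number, it is the only result described, and the measure sits in a list of outcomes to be checked for normality and tested. An analyst working from the article alone has no other quantity to use.

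**Working it through.** The plan states no power, effect size, SD or prevalence for these outcomes, so there is no figure of its own to reproduce. The checks below are illustrations.

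**1. Which form is compared?** Of the outcomes listed in the Quantitative data analysis section, the two statuses are the natural target of the χ² test. Comparison of dichotomised status is therefore the best reading, though it is not spelled out.

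**2. What status cannot see.** Inputs: cut-offs of 4 (SARC-F, range 0 to 10) and 3 (PRISMA-7, seven items; I assume one point per item, so 0 to 7).
- SARC-F 8 to 6: both values are at least 4, so no change. SARC-F 3 to 1: both are below 4, so no change.
- Largest invisible improvement on SARC-F: 10 to 4, which is 6 points. On PRISMA-7: 7 to 3, which is 4 points.
- SARC-F 4 to 3 is one point and counts as a change of status.

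**3. Efficiency of status relative to the score.** For a small shift in a normal variable, with a share p above the cut-off and z the corresponding normal quantile, relative efficiency = φ(z)² / [p(1 − p)]. The documents do not give p, so a range is shown. The equivalent number is 30 × efficiency.

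| p above cut-off | Efficiency | Loss | Equivalent n of 30 |
|---|---|---|---|
| 50% | 0.637 | 36% | 19.1 |
| 40% | 0.622 | 38% | 18.7 |
| 30% | 0.576 | 42% | 17.3 |
| 20% | 0.490 | 51% | 14.7 |
| 10% | 0.342 | 66% | 10.3 |
| 5% | 0.224 | 78% | 6.7 |

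Worked case, p = 50%: φ(0) = 0.399, and 0.399² / 0.25 = 0.637. The table is symmetric in p and 1 − p.

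**4. Why the EQ-5D-5L profile is not a numeric outcome.** I assume five levels per dimension, hence 5⁵ = 3,125 profiles.
- 21111 − 11111 = 10,000, but 11112 − 11111 = 1, although each is a one-level change.
- 12222 is numerically lower (better) than 21111, although it is worse on four dimensions and better on one.
- With all profiles weighted equally, the first digit carries 10,000² / (10,000² + 1,000² + 100² + 10² + 1²) = 99% of the variance.
- Correlation of the code with the sum of levels: 11,111 / √(5 × 101,010,101) = 0.49. About 29% of profile pairs with different level sums are ranked in the opposite order.
- As a category, 3,125 possible states cannot be tested usefully in 30 people.

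**The case against.** The strongest reply is that status may be no more than a label for the construct, parallel to quality of life for EQ-5D-5L in the same sentence. The article gives the SARC-F range, never excludes the total scores, and plans a normality check on every outcome, which makes sense only for scores. Published cut-offs are also the conventional way to use screening tools. This stands in part: it would be wrong to say that the article defines SARC-F only as a status. But the abstract and the analysis section both use status, and χ² has no more natural target among the outcomes, so the wording needs settling.

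On EQ-5D-5L, a reader might infer that the plan will run a t-test or Mann-Whitney test on the 5-digit code. The documents do not support that. The description of the profile is correct in itself, the analysis section never says that the code enters any test, and the choice of index or value set is commonly left to a full protocol or SAP that is not shown. What remains is a request for clarification.

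A reader might also infer that most of the score information is lost. That holds only if roughly 20% or fewer, or 80% or more, are above the cut-off, and the documents do not give the share.

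**Conclusion.** The point holds for SARC-F and PRISMA-7 on the best reading of the analysis section. Comparing status ignores all change within either side of the cut-off and yields no SD of score change for the later trial. The illustrative loss of 36% to 78% rests on a small normal shift and an assumed prevalence. Real scores are discrete and may be skewed, so the range shows an order of size and is not a prediction. Thirty is the recruitment target, so dropout would lower the equivalent numbers further.

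The EQ-5D-5L part is minor. The profile is unsuitable as a number, but the article does not say that it will be used as one.

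All of this concerns secondary outcomes of an uncontrolled feasibility study. The primary conclusions on volunteer recruitment and retention, session delivery, adherence and fidelity are unaffected.

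**What to change.** In the Quantitative data analysis section:

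- Name the within-person change in SARC-F total score and in PRISMA-7 total score from baseline to 6 months as the main comparison for these outcomes. Report each with a 95% CI and the SD of change.
- Keep sarcopenia status (4 or more) and frailty status (3 or more) at both time points as a supporting table.
- State that the EQ-5D-5L profile is descriptive only, and that the comparison uses an index value from a named value set or the levels on each dimension.

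The questionnaires, visits and sample size do not change. The cost is a few lines of wording and slightly more analysis.
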